# Method

## Study design

The proposed study will use a two-arm withdrawal open-label design, following the advice of Hersen and Barlow (1976) on how to evaluate the effect of drug interventions on behaviour using a single-case approach. In particular, the study will have two groups, and participants will be randomized in equal numbers to either group 1 or group 2 by means of a randomized block procedure.

There will be five study phases:

1. Study period 1: Online screening and baseline assessment: Participant children will be screened for eligibility (see below) by providing information regarding their demographics as well as completing measures assessing emotion dysregulation and irritability. If they are eligible, they and their parent(s) will meet with the study coordinator [name] at Te Puna Toiora during the week before the intervention period starts. During that meeting, eligibility will be checked, questions about the research answered, consent obtained, and the participant will complete a baseline assessment. In case the participants cannot be met in person (e.g., due to COVID-19 or because they live outside of Christchurch), meetings will be held and consent conducted over the phone or online (via Skype/Facetime/Whatsapp/Zoom). Consent forms can be uploaded and emailed/mailed back to Te Puna Toiora. Once consent is given, baseline data will be collected by means of an online survey (Qualtrics) including various psychometric measures (see below). Participants in group 1 will be given one month’s supply of Lightning Stiks^TM^ immediately after the baseline assessment. If participants cannot be seen face-to-face, the Lightning Stiks^TM^ will be delivered by courier. Those randomised to group 2 will have a delayed 4 week start (see Figure 1)
2. Study period 2: Group 1 will start taking the intervention for 4 weeks (ON-phase). Every two weeks, the parents will fill out various psychometric questionnaires assessing their children’s emotion dysregulation and irritability (see measures below), other symptoms linked to ADHD, sleep, diet, mood, anxiety and stress. Group 2 will be in a delayed baseline phase during study period 1, but will be monitored by answering the same psychometric questionnaires as group 1 every two weeks.
3. Study period 3: The intervention in group 1 will be withdrawn for four weeks (OFF-phase), whereas group 2 starts taking the Lightning Stiks^TM^ (ON-phase). Both groups answer the same questionnaires as before every two weeks.
4. Study period 4: Group 2 stops taking the interventions (OFF-phase) whereas group 1 starts taking them for another 12 weeks (ON-phase). Both groups answer the same questionnaires as before every two weeks.
5. Study period 5: When Group 1 has been taking the Lightning Stiks^TM^ for four weeks, Group 2 starts taking the multinutrient intervention for another 12 weeks and will answer questionnaires every two weeks.

Every four weeks, the children’s parents and children will meet with the study coordinator at *Te Puna Toiora* to complete various psychometric questionnaires assessing their children’s behaviour, including hyperactivity/impulsivity, inattention, emotion dysregulation, irritability, sleep, social relationships, diet, and side effects. If participants cannot be met in person, the meeting will be held via Zoom. Both the child and the parent will answer the questions of the Measure it Yourself Medical Outcome Profile (MYMOP) (see below) jointly; otherwise, they will answer the questionnaires on their children’s or their own behalf. In addition, questionnaires assessing emotion dysregulation and irritability will also be emailed to another adult who is close to the child, such as a grandparent, aunts/uncles, or teachers, twice over the period whole study period. Please find a diagram with all study phases below.

#### **Participant recruitment**

Participants will be recruited nationally across New Zealand, mainly by self-referrals following online advertisement on social media. Specifically, recruitment will take place through advertisement on Facebook (via the Mental Health and Nutrition Research Lab Te Puna Toiora account, the University of Canterbury Student Association (USCA) noticeboard), and Instagram (via the Te Puna Toiora account). Further, advertisement posters and brochures will be distributed around the UC campus, with local General Practitioners and mental health service providers. To increase Māori participation in the study, efforts will be made to engage with Māori service providers.

*Sample size*

Forty participants will be sought for the study, split 20:20 between group 1 and 2 . This number of participants is considered a sufficient sample size to determine whether the Lightning Stiks^TM^ are successful in reducing emotion dysregulation with sufficient power. This is a reasonable expectation as it allows for an adequate number of successful replications between participants, following the What Works Clearinghouse Standards for single-case designs (Handbook, n.d.).

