These beneficial effects are underlined by recent evidence, illustrating the positive effect of broad-spectrum micronutrients on a variety of mental conditions and psychological symptoms, including emotion dysregulation and irritability (Rucklidge et al., 2019; Rucklidge et al., 2014; Julia & Kaplan, 2013). For instance, Rucklidge et al. (2018) conducted a double-blinded RCT with 93 7-to-12-year-old children with ADHD, with some children having severe problems with emotional dysregulation and aggression. A clinician rating of global functioning (based on consideration of parent, teacher and child reports) showed that nearly double the number of children in the micronutrient group were identified to be ‘much’ to ‘very much’ improved relative to the placebo group (47% versus 28%). In comparison with the placebo group, children who took the micronutrients showed a greater improvement in aggression (*d* = 0.52), emotionally dysregulated behaviour (*d* = 0.66), dysregulated mood (*d* = 0.35), conduct problems (*d* = 0.48), and problem behaviour based on the parent- (*d* = 0.41) and teacher-rated (*d* = 0.45) questionnaires, although it is important to note that not all the group differences were statistically significant.

Further, in an open label, on-off-on-off (reversal design) study, 14 children with a diagnosis of ADHD between 8 and 12 years old were assessed over a period of 6 months. In particular, children were given micronutrients for 8 weeks, then the treatment was withdrawn for 4 weeks, then reintroduced for 8 weeks, and withdrawn again for 4 weeks (Gordon et al., 2015). In the treatment phases, participants showed a large and statistically significant improvement across a variety of symptoms, including issues with social behaviour and conduct problems, which are symptoms frequently related to emotion dysregulation. In addition, over two-thirds of the participants were identified as ‘much’ or ‘very much’ improved after the second treatment phase. This beneficial effect was reversed when the treatment was withdrawn, which illustrates the potential benefits of micronutrients on behavioural regulation.

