As mentioned above, emotion regulation/emotion dysregulation is frequently associated with stress, and stress is linked to various adverse effects, including the development of cardiovascular disease, atherosclerosis, oxidative stress, and inflammatory reactivity (Huang, Webb, Zourdos, & Acevedo, 2013), as well as poorer mental wellbeing, and academic underachievement (Myers et al., 2012). As an attempt to reduce stress as well as trial a new delivery modality for the micronutrients, an unpublished randomized, double-blinded trial conducted in Te Puna Toiora investigated the effect of this delivery modality on stress and mental wellbeing in UC students. The product tested was powdered multinutrient straws called EMPowerplus Lightning Stiks^TM^, which use Direct-to-Mouth technology in which the multinutrients are absorbed through the tissues of the mouth. This different modality means that the dose of the micronutirents is much lower than has been previously used in other research on broad spectrum micronutrients. Indeed, all doses are well below the recommended Dietary Allowance (RDA) and none are given in a dose above the Upper Limit (UL). None of the doses are given at a medicinal level. The Lightning Stiks^TM^ consist of a blend of 36 ingredients, including vitamins, minerals and amino acids, called EMPowerplus, and previous research has shown that this formula (taken in capsules) can improve stress, anxiety, and mood in adults as well as in children (J. J. Rucklidge et al., 2012; J. J. Rucklidge & Blampied, 2011; Sole, Rucklidge, & Blampied, 2017; Stough et al., 2011). Preliminary data analysis of this trial (STAR trial - not yet published) revealed that the Lightning Stiks^TM^ reduced stress in students more rapidly relative to the placebo group, although the group difference was not statistically significant (*d* = 0.39, *p* = .108). Additionally, the multinutrient group displayed a greater beneficial impact on emotion regulation and irritability compared to the placebo group (*d* = 0.54, *p* = .024), as well as reduced symptoms of anger (*d* = 0.62, *d* = .011).

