**Hypotheses:**

1. The Lighting Stiks^TM^ will be found to be an acceptable and effective intervention to reduce irritability, behavioural- and emotional dysregulation in 5-10 year-old children.

2. The beneficial effect of the micronutrients will be present during the phases where participants take the micronutrients, and diminish during phases where the treatment is withdrawn.

3. There will be differences in the first month between the two groups in emotion dysregulation when group 1 will be taking the nutrients and group 2 will not (see design), with group 1 showing better emotion regulation than group 2.

4. There will be differences in the second month between the two groups in emotion dysregulation when group 2 will be taking the micronutrients and group 1 will not, with group 2 showing better emotion regulation than group 1.

5. There will be differences in the third month between the groups in emotion dysregulation when group 1 will be taking the micronutrients and group 2 will not, with group 1 representing better emotion regulation than group 2.

6. During the final eight weeks of the trial, when both groups will take the nutrients simultaneously, both groups will display similar competencies in emotion regulation.

7. It is expected that the improved behaviour in children will reduce the parents’ symptoms of stress, potentially having an additional beneficial effect on the children’s behaviour.

8. The Lightning Stiks^TM^ will be found to be a safe intervention that has a low incidence of side effects which will be mild in severity and only last temporarily, and yields high consumer satisfaction in the participants.

9. The longer the participants take the Lightning Stiks^TM^ continuously at a time, the greater the beneficial effect on emotion dysregulation.

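### The unqualified claim of sufficient power for 40 children rests on single-case replication and does not cover the between-group hypotheses 3 to 5

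*Protocol*

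**What the plan says.** The Protocol, Participant recruitment (Sample size), sets the number: "Forty participants will be sought for the study, split 20:20 between group 1 and 2". It says this number is enough to determine whether the Lightning Stiks "are successful in reducing emotion dysregulation with sufficient power". The reason offered is that "it allows for an adequate number of successful replications between participants", with reference to published standards for single-case designs. No planning effect, standard deviation, significance level, sidedness, power value or dropout allowance accompanies the claim.

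The Hypotheses section contains three comparisons of one randomised group with the other, one per month. Hypothesis 3 reads "There will be differences in the first month between the two groups in emotion dysregulation" and gives a direction, "with group 1 showing better emotion regulation than group 2". Hypotheses 4 and 5 have the same form for months two and three. The Nomothetic analysis section plans hierarchical linear modelling to complement the individual-level analysis.

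The Background cites between-group effects on related outcomes. For this product in university students, against placebo, it reports "emotion regulation and irritability compared to the placebo group (*d* = 0.54, *p* = .024" and d = 0.62 for anger. For children with ADHD in a placebo-controlled micronutrient trial it reports "emotionally dysregulated behaviour (*d* = 0.66), dysregulated mood (*d* = 0.35", and d = 0.52 for aggression.

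**The concern.** A replication count and a power statement answer different questions. Replication under single-case standards concerns how often a phase change produces the expected shift within a child. It says nothing about the precision with which 20 children can be compared with 20 others. Because the power sentence is not restricted to within-child contrasts, a reader will apply it to hypotheses 3 to 5 as well.

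If those comparisons come out non-significant, a trial described as adequately powered invites the conclusion that the groups did not differ, when the data may simply have been too imprecise to tell.

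**Working it through.** **No figure to reproduce.** The protocol gives no numerical power and no inputs from which 40 could be derived. The check therefore asks what 20 per group delivers.

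**Inputs from the protocol.** n = 20 per group (Participant recruitment). Effects d = 0.35, 0.52, 0.54, 0.62 and 0.66 (Background). Test-retest ICC of the CL-ARI, 0.67 (Assessment Tools), used only as a stand-in for the baseline to follow-up correlation.

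**Assumptions, none stated in the protocol.** Two-sided 5% test, no dropout, standardised outcome (SD = 1).

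**1. Unadjusted comparison of 20 with 20.** Noncentrality = d × √(n/2) = d × √10 = 3.162 d. There are 38 degrees of freedom and the critical t is 2.024. Power comes from the noncentral t distribution.

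| d | Noncentrality | Power, two-sided | Power, one-sided |
|---|---|---|---|
| 0.35 | 1.11 | 19% | 29% |
| 0.52 | 1.64 | 36% | 49% |
| 0.54 | 1.71 | 38% | 51% |
| 0.62 | 1.96 | 48% | 61% |
| 0.66 | 2.09 | 53% | 66% |

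Solving for 80% power gives a detectable d of 0.91 two-sided, or 0.80 one-sided. In the other direction, 80% power two-sided would need 55 per group at d = 0.54 and 38 per group at d = 0.66.

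**2. Dropout.** At d = 0.54, power falls to 35% with 18 per group and to 32% with 16 per group.

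**3. Baseline adjustment.** Adjusting for a baseline value with correlation r replaces d by d/√(1 − r²) and multiplies the detectable difference by √(1 − r²).

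| r | √(1 − r²) | Power at d = 0.54 | Power at d = 0.66 | Detectable d, 80% power |
|---|---|---|---|---|
| 0.5 | 0.866 | 48% | 65% | 0.91 × 0.866 = 0.79 |
| 0.67 | 0.742 | 61% | 78% | 0.91 × 0.742 = 0.68 |
| 0.8 | 0.600 | 79% | 92% | 0.91 × 0.600 = 0.55 |

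**4. The within-child contrast that the replication argument does concern.** Periods 2 and 3 form an ON/OFF versus OFF/ON sequence. With within-child correlation ρ and no carryover, the standard error of the treatment effect is √[(2(1 − ρ)/4) × (1/20 + 1/20)].

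- ρ = 0.5: √(0.25 × 0.1) = 0.158. Noncentrality 0.54/0.158 = 3.42, power 91%.
- ρ = 0.67: √(0.165 × 0.1) = 0.128. Noncentrality 0.54/0.128 = 4.20, power 98%.

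The same 40 children can thus support a good within-child contrast while giving limited power for a between-group comparison in a single month.

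**The case against.** The strongest reply is that the sentence was never about hypotheses 3 to 5. The Study design section declares a single-case approach, the individual-level analysis leads, and the sample-size rationale is explicitly one of replication. On that reading the claim is loose rather than false, since the within-child contrast is well powered without carryover. This stands in part, and it is why the remedy is to restrict the claim. It does not rescue the sentence as written, which carries no such limit in a protocol that also states three group comparisons.

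A second reply is that 38% is the least favourable of several figures at d = 0.54. The protocol names no unadjusted t-test, its hypotheses are directional, and it plans a hierarchical model. That is fair, so the result is given as a range. One-sided testing still leaves every cited effect below 80%. Baseline adjustment brings d = 0.54 to about 79% only at r = 0.8, although d = 0.66 gets there at r of about 0.7.

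Third, d = 0.54 is not a planning effect. It comes from a blinded student trial, whereas hypotheses 3 to 5 compare open-label treatment with no treatment in children. Expectancy could widen the difference, and carryover could narrow it in months two and three.

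A reader might go further than the documents allow in three ways:

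- **Only the within-child contrast is well powered.** This is not shown, because power under the planned hierarchical model has not been computed.
- **A joint chance of success for hypotheses 3 to 5, found by multiplying three powers.** The same 40 children supply all three contrasts, so they are not independent, and the protocol does not require all three to be significant together.
- **Forty children are too few for the trial.** This does not follow, given the single-case aim and the exploratory description under Aims and Objectives.

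**Conclusion.** The concern holds in a limited form: the power claim is unqualified, its stated basis does not extend to hypotheses 3 to 5, and the protocol's cited effects do not support it there. Unadjusted, two-sided at 5% and without dropout, power is about 19% to 53% for d = 0.35 to 0.66, with 38% at d = 0.54. The difference detectable with 80% power, 0.91 SD, exceeds each of the cited between-group effects.

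These figures depend on assumed test settings and on effects borrowed from other populations and designs. The adjusted figures also depend on an assumed correlation, for which the ICC of 0.67 is only a proxy. The within-child figures of 91% to 98% require no carryover, and the Ideographic analysis section itself allows that effects may accumulate across phases. This should be fixed, but it does not undermine the design.

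**What to change.** In Participant recruitment (Sample size):

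1. Restrict the claim of sufficient power to the within-child ON/OFF contrast, and state that it assumes no carryover. The supporting figure is about 91% to 98% at d = 0.54 for within-child correlations of 0.5 to 0.67.
2. For hypotheses 3 to 5, state the difference detectable with 80% power: about 0.9 SD unadjusted, and about 0.7 to 0.8 SD with baseline adjustment (r = 0.67 to 0.5).
3. Give the power at the cited effects (19% to 53% unadjusted; at d = 0.54, 38% unadjusted and about 48% to 61% adjusted), together with the significance level, sidedness, dropout and correlation assumed.
4. Label hypotheses 3 to 5 exploratory, and say that a non-significant result on any of them is inconclusive.

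The cost is wording only. The number of children, the design and the analyses stay as they are. The price is a less favourable statement of power for the group comparisons.

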#### Inclusion Criteria:

1) Participants must be between 5 and 10 years of age, 2) able to ingest 1 Lightning Stik^TM^/day), 3) the children’s parents need to have English language competence sufficient to understand study materials to answer questionnaires, 4) the children need to have English language competence sufficient to understand and answer the questions asked in the child-related measure, 5) participants need to have at least mild-to-moderate levels of emotional dysregulation and irritability following the Affective-Reactivity-Index (ARI), represented by a total score of 3 or higher.

#### Exclusion criteria:

1) Taking psychotropic medications (e.g., Ritalin) in the prior 4 weeks before for the trial period. 2) presence of any serious medical or psychiatric condition that might require hospitalization, 3) any known allergies to the ingredients of the Lightning Stiks^TM^.

#### Product and dosing:

The product being tested is called EMP Lightning Stiks^TM^ which come as powdered straws that use Direct-to-Mouth technology, which means all the participants have to do is put the powder directly in their mouth and let it dissolve (rather than swallowing it). The Lightning Stiks^TM^ consist of a blend of 36 ingredients, including vitamins, minerals and amino acids. The advantage of this mode of delivery is that the doses of the ingredients are much lower than those found in capsules and well below the RDA - as such, no ingredient is given in a medicinal dose. Because the doses are all below RDA, safety concerns for any of the proposed ingredients are unlikely. Further, all doses are well below the Tolerable Upper Intake Limit (UL), which is considered the highest amount of daily nutrient intake that is not likely to cause any adverse effects (Nutritional Institutes of Health, n.d.). In addition, as the Lightning Stiks^TM^ are available in various flavours, such as Tropical Punch, Banana, and Sour Berry, they do not have the usual unpleasant smell or taste that multinutrients usually do, and no swallowing capsules is necessary, which is why they might be a convenient alternative treatment for children. In the proposed study, children will be able to choose which flavour they would like to try during the study. If the child would like to change the flavour of the Lightning Stiks^TM^ during an ON-phase they are welcome to do so.

Participants are asked to take one Lightning Stik^TM^ a day; however, as anecdotal reports have previously reported headaches in the first few days of taking the Lightning Stiks^TM^, participants are advised to start with only ½ a straw in this study for the first two days.

### Assessment Tools

An on-line survey created with Qualtrics will ask the participants and their parents to complete measures of emotion dysregulation, irritability, inattention, hyperactivity/impulsivity, diet, sleep, depression, anxiety and stress. The measures that are proposed in this study are standard measures used in clinical trials. In addition, the study coordinator will meet with the participants once a month in person at Te Puna Toiora to collect data on emotion dysregulation, mood, side effects, and interpersonal skills. If participants cannot be met in person, these meetings will be held via Zoom or other online platforms.

Primary outcome measures

*Clinician-administered:*

*The Clinician Affective Reactivity Index (Parent/Child Interview Guide) (CL-ARI):* This scale is a parent-report measure that assesses emotion regulation and irritability in children over the past week, looking at temper outbursts and irritable mood, and their frequency, severity, and duration. Further, it assesses whether the child’s irritable behaviour causes problems in the family, impairments in school, and assesses potential improvements over time. The CL-ARI has good internal consistency (*α* = .89) and adequate test-retest reliability (*ICC* = .67) (Haller et al., 2020). In the proposed study, the study coordinator will meet the parent and the child every four weeks to collect data on the CL-ARI in person.

*Clinical Global Impressions - Improvement Scale (CGI-I) (Guy, 1976):* The CGI-I is a clinician-administered scale that rates, based on all information obtained from all raters (parents, child and significant other) how much better/worse the participant is functioning since baseline across irritability/emotion dysregulation, mood, stress, energy, and sleep. Each item has seven responses, ranging from “very much improved” (1) to “very much worse” (7) and helps to provide a brief, overall assessment of the participant. The CGI-I is not used during baseline assessment. The CGI-I has demonstrated high external validity (*r* = 0.74) (Kadouri et al., 2007) and is widely used in clinical trials.

Secondary outcome measures

*Clinician-administered:*

*Clinical Global Impressions – Severity Scale (CGI-S) (Guy, 1976)* is a clinician-rated evaluation of symptom severity by means of the question: “Considering your total clinical experience with this particular population, how impaired is the patient at this time?” The item is scored on a 7-point Likert scale, ranging from 1 (normal, not impaired) to 7 (markedly impaired) (Busner, 2007). The CGI-S is commonly used in clinical trials and has shown to be sensitive to clinical change in diagnostically diverse populations. In the proposed study, it is administered during the baseline assessment and at the end of the study, giving an overall impression of the participants’ functioning before and after the intervention.

*Parent- or other-adult administered:*

*Affective Reactivity Index (ARI) (Parent version)* (Stringaris et al., 2012): The ARI is a concise, parent-rated scale assessing the child’s irritability. It incorporates seven items that ask about feelings of irritability during the past seven days (e.g., “My child is easily annoyed by others”, “My child gets angry frequently”, “Overall, irritability causes my child problems”). How true a statement is can be scored on a 0 (not true) to 2 (certainly true) Likert scale. It has been shown to have good internal consistency (*α* = .84 - .92) (Ezpeleta et al., 2020) and is considered an appropriate measure to assess irritability (Stringaris et al., 2012).

*Strengths and Difficulties Questionnaire (SDQ)* (Goodman, 1997): The Strength and Difficulties Questionnaire consists of 25 items across five subscales, measuring emotional symptoms, conduct problems, hyperactivity/inattention, peer relationship problems, and prosocial behavior in 4-17 year old children and adolescents (Stone, Otten, Engels, Vermulst, & Janssens, 2010). Each item is scored on a 3-point Likert scale (‘not true’, ‘somewhat true’, and ‘certainly true’) by the child’s parents. Scores between 0-13 are considered normal, whereas scores between 17-40 represent severe psychological symptoms.

The SDQ also looks at how severely the observed symptoms interfere with family relationships, friendships, learning in the classroom, and leisure activities. This ‘impact score’ is assessed by means of a 0 to 4 Likert scale (‘not at all’ to ‘a great deal’), with a score of 2 or greater representing problems in such areas (Gordon, Rucklidge, Blampied, & Johnstone, 2015). The SDQ is considered sufficiently internally consistent for the total difficulties scale (*α* = 0.78) as well as for the emotional problems subscale (*α* = 0.73). However, for the hyperactivity-inattention and prosocial behaviours its internal consistency is moderate (*α* = 0.69 and *α* = 0.63 respectively), and poor for peer and conduct problems (*α* = 0.57 and *α* = 0.47 respectively) (Bøe, Hysing, Skogen, & Breivik, 2016).

*Adapted Clinical Global Impressions Improvement Scale (CGI-I_Parent_) (Guy, 1976):* The original CGI-I was a clinician-administered scale that rates how much better/worse the participant is since participation in the trial across irritability/emotion dysregulation, mood, stress, sleep, and energy. Each item has seven responses, ranging from “very much improved” (1) to “very much worse” (7) and helps to provide a brief, overall assessment of the participant. In the proposed study, the CGI-I will also be adapted so that it represents the parent’s perception of change in their children’s behaviour (CGI_I_Parent_). In the proposed study, the CGI-I is not used during baseline assessment. The CGI-I has demonstrated high external validity (*r* = 0.74) (Kadouri et al., 2007) and is widely used in clinical trials.

*The Child Swanson, Nolan, and Pelham-IV Questionnaire (SNAP-IV) (Swanson, 1992; Swanson et al., 1983):* The child SNAP-IV assesses symptoms of ADHD and oppositional defiant disorder (ODD) in children every 4 weeks. It is a parent- and teacher-rating scale that has three subscales: inattention (item 1-9), hyperactivity-impulsivity (item 10-18), and symptoms of ODD (item 19-26), which are each scored on a 4-point Likert scale (‘not at all’, ‘just a little’, ‘quite a bit’, and ‘very much’). The SNAP-IV displays high internal consistency (*α* =.94) and sufficient interrater reliability and test-retest reliability (*r* =.43-.49) (Bussing et al., 2008). In the proposed study, the SNAP-IV will be emailed to another significant adult in the children’s life, for example aunties/uncles, grandparents, or teachers (in addition to the parent) at baseline and during the last month where participants take the nutrients.

*The Children’s Sleep Habits Questionnaire (CSHQ) (Owens et al., 2000):* The CSHQ is a parent-rated measure that assesses sleep in school-aged children. It consists of eight subscales that are both scored individually and make up a total score, identifying sleep problems. In the proposed study, only the total score will be reported, with a score of 41 (larger = more severe) representing the clinical cut-off score for sleep problems. Larger scores indicate more severe sleeping problems. The CSHQ has sufficient internal consistency (*α* = 0.68-0.78), adequate test-retest reliability (*r* = 0.62-0.79), a sensitivity of 0.80, and a specificity of 0.72 (Owens et al., 2000).

*Eating Behaviour Questionnaire (Baker et al., 2003)*: By means of a dietary questionnaire the parent’s and child’s general diet and eating behaviour is assessed. In particular, parents fill out various questions representing their and their child’s diet and eating pattern, including how many servings of fruit and vegetables they eat per day, how much food they eat per meal, how regular they eat, and how frequently they eat processed foods and fast-food. Lastly, participants are asked to rate their diet on a scale of 1 (not very healthy) to 7 (very healthy). The total score ranges from 9-47, and a higher score represents a healthier diet. Parents answer the dietary questionnaire during the first and the last study phase.

*Abbreviated Acceptability Rating Profile (AARP) (Tarnowski & Simonian, 1992).* At the end of the trial, parents will be asked whether they perceive the Lightning Stiks^TM^ as a helpful and acceptable treatment to reduce the children’s irritability and emotional dysregulation by means of the AARP. The AARP is a parent-administered, 8 item rating-scale, with each item being scored on 6-point Likert scale (1 = ’strongly disagree’ to 6 = ‘strongly agree’) asking about the child’s treatment acceptability, likeability, effectiveness, and helpfulness of the intervention. The AARP has shown to have excellent internal consistency (*α =* .95-.98) and adequate discriminant validity (Tarnowski & Simonian, 1992).

*The Depression Anxiety and Stress Scale-21 (DASS-21):* The DASS-21 is the shorter, 21-item of the original 42-item DASS-42 (Lovibond and Lovibond, 1995). It is a publicly available questionnaire, which assesses an individual’s symptom severity associated with depression, anxiety and stress using a 0 – 3 Likert scale. Cut-offs have been provided to indicate normal, mild, moderate, severe, or extremely severe problems; anything below 10 (for depression), 8 (for anxiety) and 15 (for stress) is considered within the normal to mild range. The scale has excellent reliability (*ICC* = .93) as well as a sufficient construct validity (Henry & Crawford, 2005). In the proposed study, it is completed by the parents to measure their own’s wellbeing and stress every four weeks.

*The Side-Effect Checklist (revised) (ASEC) (Uher et al., 2009):* The ASEC will assess side effects, safety and adverse events of the intervention. The ASEC has been adapted for the purposes of this study to remove references to anti-depressants. In addition, the item regarding sexual dysfunction is removed since it is not applicable for children, and the potential adverse event ‘rash’ was added because this has been a common side effect in past studies. Side effects will be assessed every two weeks, and any concerning adverse events will be discussed with the study physician and the co-investigators. In the case of a serious adverse event, the investigators will consider whether termination of the study is necessary.

*Parent- and child administered*

*The Measure Yourself Medical Outcome Profile (The MYMOP)* (Paterson, 1996): Once a month, the research coordinator will meet with the parent and the child to collect information in person regarding the child’s symptoms, including hyperactivity, attention, impulsivity, emotion regulation, irritability, mood, and sleep by means of the MYMOP. Each symptom can be scored on a scale from 0 to 5, with a score of 0 representing no problems, whereas a score of 5 indicates that there are lots of problems. The clinician will also ask questions regarding intervention compliance (on behalf of the children, the parents will report how easy it was to remember and to take the Lightning Stiks^TM^ on a 3-point Likert scale; ‘never difficult’, ‘sometimes difficult’, and ‘always difficult’), as well as potential side-effects, which can be scored on a 5-point Likert scale ranging from major problems to no problems. The MYMOP has demonstrated adequate internal consistency and validity (Hourigan, Clarke, Whitehouse, & Challinor, 2014).

